### Interventions

The intervention will initially take place in the specific ward that receives cardiac surgery patients. Participant recruitment will begin upon the patient’s admission the day before the surgery, during which they will undergo a pre-operative assessment based on the study criteria.

Physiotherapists and physiotherapy students will receive training regarding the research protocol through two in-person sessions comprising demonstrations and didactic materials. The same therapists will be responsible for both the intervention and control groups.

Patients included in the study will undergo evaluations at two time points: pre-operatively (initial assessment) and post-operatively (five days after the pre-operative assessment).

Following the initial assessment, the patient will undergo cardiac surgery the next day and will be transferred to the ICU after the procedure. The protocol will be initiated in the ICU for all three groups of the research.

#### Control group (Usual care)

Patients undergoing standard physiotherapy treatment, consisting of a kinesiotherapy protocol. Patients will receive treatment twice a day, alternating between the treatment initiated in the ICU and progressing to the general ward. Specifically, the treatment plan is divided by days and environments, taking into consideration the general characteristic that patients are discharged from the ICU on the 2nd day of the post-operative period, and Day 1 represents the first day of post-operation:

### Day 1 (ICU)

• Diaphragmatic breathing exercises – 1 set of 10 repetitions

• Cough stimulation

• Diaphragmatic breathing exercises associated with upper limbs – Shoulder flexion/extension 2 sets of 10 reps up to 90 degrees

• Shoulder abduction 1 set of 10 reps (avoiding pain)

• Diaphragmatic breathing exercises associated with lower limbs – Thigh flexion 1 set of 10 reps

• Dorsiflexion/plantar flexion of foot 1 set of 10 reps

### Day 2 (ICU)

• Diaphragmatic breathing – 1 set of 10 reps

• Cough stimulation

• Breathing exercises associated with upper limbs – Shoulder flexion 2 sets of 10 reps

• Breathing exercises associated with lower limbs – Thigh flexion 1 set of 10 reps

• Dorsiflexion/plantar flexion of foot 1 set of 10 reps

• Cycle ergometer for 3 minutes

• Breathing exercise with incentive spirometer (SMI) 1 set of 10 reps

### Day 3 (General Ward)

• Diaphragmatic breathing – 1 set of 10 reps

• Cough stimulation

• Breathing exercises associated with upper limbs – Shoulder flexion 2 sets of 10 reps

• Breathing exercises associated with lower limbs – Thigh flexion 1 set of 10 reps

• Dorsiflexion/plantar flexion of foot 1 set of 10 reps

• Ambulation for 5 minutes

### Day 4 (General Ward)

• Diaphragmatic breathing – 1 set of 10 reps

• Cough stimulation

• Ambulation for 10 minutes

### Day 5 (General Ward)

• Diaphragmatic breathing – 1 set of 10 reps

• Cough stimulation

• Ambulation for 15 minutes

#### Intervention group 1 (CPAP)

Patients in this group will receive the same care as the control group, with the addition of Non-Invasive Ventilation (NIV) using nasal Continuous Positive Airway Pressure (CPAP) at 10 cmH2O pressure for 1 hour. The CPAP device from the brand RESMED will be used. This intervention will be administered for a duration of 5 days throughout the patient’s hospitalization, both in the ICU and general ward. The frequency of sessions will be twice (2 times) per day, in the morning and afternoon.

Flexibility in scheduling the intervention sessions is planned, considering that hospital environments often involve examinations and other procedures that might impact the initially scheduled protocol times. After the fifth day, the patient will undergo a reassessment using the same measurement instruments as before.

#### Intervention group 2 (BIPAP)

Patients in this group will receive the same care as the control group, with the addition of Non-Invasive Ventilation (NIV) using nasal Bi-Level Positive Airway Pressure (BIPAP) with an Inspiratory Positive Airway Pressure (IPAP) of 13 cmH2O and an Expiratory Positive Airway Pressure (EPAP) of 8 cmH2O for 1 hour. The BIPAP device from the brand RESMED will be used. This intervention will be administered for a duration of 5 days throughout the patient’s hospitalization, both in the ICU and general ward. The frequency of sessions will be twice (2 times) per day, in the morning and afternoon.

Similar to the CPAP group, flexibility in scheduling the intervention sessions is planned to accommodate the dynamic nature of hospital settings. After the fifth day, the patient will undergo a reassessment using the same measurement instruments as before.

### Data collection

The tests and questionnaires used for these assessments are listed along with their outcome variables in Fig 1.

**Fig 1 pone.0304569.g001:**
[figure not shown]
The recommendations for interventional trials (SPIRIT) schedule of enrollment, interventions, and assessments.

#### Clinical evaluation form

After signing the informed consent form, patients will be assessed using an evaluation form. In this form, on the first day, the assessment will encompass both anamnesis (patient history) and physical examination, with a focus on the patient’s cardiac history. This will be followed by measurements specific to the protocol, including chest X-ray, quality of life questionnaire, Timed Up and Go (TUG) test, and spirometry. The assessment may be divided into two stages if there are other demands on the patient during their hospitalization.

#### Pulmonary function

All participants will undergo an evaluation by a CONTEC model spirometer (SPB80b, CHINA) to verify lung volumes and capacities. At least three tests will be performed, with a variation of less than 5% and the highest value obtained in one of the tests will be compared with the predicted values of pulmonary function parameters for the Brazilian population. FEV1 and FVC will be assessed. The predicted values will be calculated using the reference values [17].

#### Length of hospital stay

Absolute number of days of hospitalization up to 2 weeks after the date of randomization.

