**Primary outcomes:**

Pulmonary function, Length of hospital stay.

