### Post-randomization exclusion criteria

Undergoing hospital-based treatment contraindicating study participation (e.g., pacemaker implantation, pneumothorax requiring thoracic drainage).Death or other decompensations unrelated to the research.Return to the ICU.

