#### Other variables

Will be collected through the analysis of the patient’s medical records, including the type of surgery, personal history, pre-operative ejection fraction, BMI, gender, and age.

*Adherence*. During the assessment and daily sessions, therapists will be instructed to raise awareness, provide guidance, and explain the purpose of the research to ensure maximum adherence to the protocol. Adherence assessment will involve direct communication between the researcher and the participating physiotherapists and students, facilitated through a dedicated messaging app group created for this purpose. Monitoring adherence will also include regular visits by the researcher during the application of the protocol treatment.

*Concomitant care*. Patients requiring extended ICU stays with the use of more advanced devices for prolonged non-invasive ventilation or even the return to invasive mechanical ventilation during the study period will be considered non-adherent from that point, and thus an intention-to-treat analysis will be employed.

*Risks and adverse effects*. Throughout the treatment, there are minimal risks of cardiac arrhythmias, decreased oxygen saturation levels, shortness of breath, bronchospasm, dizziness, syncope, hypotension or hypertension, altered heart rate, or chest pain. Throughout the entire duration, patients will be continuously monitored for vital signs.

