### Statistical analysis

The data will be analyzed using IBM SPSS Statistics Base 25.0 software for Windows. The normality of variables will be assessed using the Shapiro-Wilk test. The paired Student’s t-test will be utilized to compare data before and after the intervention. Linear Mixed Effects Models will be used for longitudinal data analysis. The effect of NIV (CPAP or BIPAP) combined with usual physiotherapy over time will be compared between groups using generalized linear mixed models (GLMMs), they can account for the correlation between repeated measurements within the same individual, which is important in longitudinal studies. The intention-to-treat (ITT) approach will be used to handle potential missing data. Time dependence is a key consideration in data analysis, and autoregression, particularly Integer Auto Regressive (INAR) models, is a valuable method for modeling this. However, selecting the appropriate autoregressive model is essential for gaining insights into the temporal dynamics of medical outcomes. Fixed effects models as a choice for addressing endogeneity. We use technique Bayesian model averaging to select relevant variables while controlling for overfitting. To ensure analysis accuracy, parametric model assumptions, such as homoscedasticity and residual normality, will be checked. Moreover, various models will be considered to accommodate specific data characteristics, such as skewness and zero-inflation/overdispersion.

Effect sizes will be calculated using Cohen’s d. Continuous variables will be reported as mean ± standard deviation (SD) along with a 95% confidence interval (CI), while categorical variables will be presented as absolute frequencies and percentages. The significance level will be set at 5% for all analyses (p ≤ 0.05).

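### Primary length of stay is counted only to two weeks after randomisation, with no counting origin and no death rule, while deaths and ICU returns are excluded after randomisation despite intention to treat

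*Protocol article*

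**What the plan says.** The abstract of the protocol article lists the primary outcomes as "Pulmonary function, Length of hospital stay". The section on length of hospital stay consists of one sentence: "Absolute number of days of hospitalization up to 2 weeks after the date of randomization". It names an end to the window, but no first day, no end event such as live discharge, and no value for a patient who dies.

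Four other places bear on this outcome:

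- **Post-randomization exclusion criteria** list "Death or other decompensations unrelated to the research.Return to the ICU".
- **Statistical analysis** states "The intention-to-treat (ITT) approach will be used to handle potential missing data". Under concomitant care, in **Other variables**, patients with prolonged ICU ventilation "will be considered non-adherent from that point, and thus an intention-to-treat analysis will be employed".
- **Entry.** The Interventions section says "Participant recruitment will begin upon the patient’s admission the day before the surgery", whereas the inclusion criteria describe people who have already been operated on and are stable. Neither place fixes the day of randomisation.
- **Presence of lung complications**, a secondary outcome, names death from any cause in its time frame. Length of stay does not.

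**The concern.** Three gaps sit in the definition of a primary outcome.

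1. **Window.** Discharges after day 14 are not observed. The Introduction gives fewer intubations, shorter stays and fewer pulmonary complications as the aims of prophylactic NIV. Complicated courses are where long stays arise, and the window cannot tell them apart.
2. **Death.** Under the post-randomisation exclusions, a death judged unrelated to the research leaves the analysis, as does a patient who returns to the ICU. Under intention to treat they stay in, but then a death on an early day counts as a short, favourable stay. The document supports both routes, and neither treats death as the bad outcome it is.
3. **Origin.** Days could be counted from admission, surgery or randomisation. Since entry is described both before and after surgery, the end of the window is not a fixed postoperative day either.

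At stake are the size of the estimated difference in days and whether each arm's worst courses are represented in it.

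**Working it through.** **Inputs from the protocol:** 21 patients per arm, 63 in total; a 14-day limit. The sample size was set on pulmonary function, so there is no planned figure for length of stay to reproduce. The protocol gives no distribution of stay and no mortality.

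**Assumptions (not from the protocol):** log-normal stay with median m and log-SD s; NIV shortens every stay by 20%; longer stays contribute 14 days.

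**Formulas.** With d = ln(14/m)/s:

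- share beyond day 14 = 1 − Φ(d)
- mean stay E = m·exp(s²/2); true difference = 0.2·E
- mean of stay limited to 14 = E·Φ(d − s) + 14·(1 − Φ(d)); limited difference = this value at m minus this value at 0.8m

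**Example, m = 10, s = 0.5.** d = ln(1.4)/0.5 = 0.673, so 25.0% exceed 14 days. E = 11.33, so the true difference is 2.27. The limited means are 9.95 (m = 10) and 8.48 (m = 8), a difference of 1.47. Loss = 1 − 1.47/2.27 = 35%.

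| Median, log-SD | Beyond day 14 | True difference (days) | Limited difference | Loss |
|---|---|---|---|---|
| 7, 0.3 | 1.0% | 1.46 | 1.45 | 1% |
| 8, 0.5 | 13.2% | 1.81 | 1.44 | 20% |
| 10, 0.35 | 16.8% | 2.13 | 1.74 | 18% |
| 10, 0.5 | 25.0% | 2.27 | 1.47 | 35% |
| 12, 0.4 | 35.0% | 2.60 | 1.56 | 40% |
| 12, 0.5 | 37.9% | 2.72 | 1.38 | 49% |

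**Power.** Simulated two-sided 5% t-test, 21 per arm, 20,000 trials, unlimited versus limited: 0.50 vs 0.51 (10, 0.35), 0.27 vs 0.28 (10, 0.5), 0.40 vs 0.40 (12, 0.4). A rank test gives 0.50 vs 0.50, 0.28 vs 0.27 and 0.41 vs 0.39. The limit shrinks the SD along with the difference.

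**Effect only on long stays.** If NIV halves just the part of a stay beyond day 14, the saving is half of (E minus the limited mean). For (10, 0.5) that is (11.33 − 9.95)/2 = 0.69 day; for (10, 0.35) it is 0.26 and for (12, 0.4) 0.84. The 14-day measure records exactly zero in each case.

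**Death.** One death recorded as 4 days instead of 10 moves an arm mean by (10 − 4)/21 = 0.29 day in the favourable direction. With survivors averaging 8 days and one death on day 3, the arm mean is (20 × 8 + 3)/21 = 7.76 if the death counts as a stay, 8.00 if it is dropped, and (20 × 8 + 14)/21 = 8.29 if it is set to 14. At an assumed mortality of 2% to 5%, the chance of at least one death among 63 is 1 − 0.98^63 = 72% to 1 − 0.95^63 = 96%.

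**The case against.** The strongest reply is that the sentence describes an observation window, that a fixed window is legitimate, and that death handling belongs in the analysis plan, which is not shown. The first two parts stand: time to discharge censored at day 14 would be sound. But the article does not say that this is the analysis. The missing origin lies in the outcome definition itself, and the clash between the exclusions and intention to treat is within this one document.

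Several stronger readings are tempting and should be resisted:

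- **That longer stays are recorded as 14 days, or that the count starts at randomisation.** The text says neither. Randomisation fixes only the end of the window.
- **That the loss is one third to one half.** At median 10, that figure needs an added floor of 7 days (2.13 falls to 1.42 and 2.26 to 1.11). No section records shorter stays as 7. The Interventions section places reassessment five days after the preoperative assessment, which is earlier than the floor assumes, and redefining the outcome would not remove a minimum stay anyway.
- **That the trial loses power.** For a proportional effect it does not.
- **That deaths could reverse the result.** At 0.29 day per death, cancelling limited differences of 1.47 to 1.74 days takes 5.1 to 6.1 excess deaths in one arm of 21. Even with the floor it takes 1.11/0.286 = 3.9. The documents give no mortality that would make this likely.
- **That mean, SD and Cohen's d must go.** The Statistical analysis section also plans assumption checks and models for skewness, so this is largely preference.

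An ambiguity of a day or two in the origin would also fall on all arms alike; it matters mainly for interpretation and reproducibility.

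**Conclusion.** The point holds as a defect in the definition of a primary outcome. Followed literally, the plan leaves stays beyond day 14 unmeasured, does not say where counting starts, and either removes certain deaths and ICU returns after randomisation or lets an early death count as a short stay.

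Its size rests on assumed distributions. For medians of 7 to 12 days and log-SDs of 0.3 to 0.5, about 1% to 35% of stays pass day 14 and a 20% shortening is understated by about 1% to 40%; the single most extreme pairing (12, 0.5) gives 38% and 49%. If stays are short, the window hardly matters, but the death, exclusion and origin gaps remain. The harm is an understated difference in days and blindness to effects on long stays, not lost power for a proportional effect. The point deserves correction; it does not show that the trial's conclusion would reverse.

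**What to change.** - Define the outcome as days from surgery, as the one named origin, to discharge alive, for all randomised patients, including those now listed under the post-randomisation exclusions. Reconcile the inclusion criteria with the Interventions section so that the day of randomisation relative to surgery is stated.
- Read the discharge date from the hospital record without a 14-day limit. Alternatively, keep the window and censor at day 14 from the named origin.
- Treat in-hospital death as a competing event for live discharge, or give it the worst rank.
- Compare arms with a time-to-live-discharge or rank-based analysis, and report median and IQR beside the mean.

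**Cost.** The change is wording plus a documented update of the outcome definition; the Protocol modifications section rules out changes after registry publication, so the update must be made openly. If the limit is lifted, later discharge dates are needed for patients still in hospital at day 14. With one control arm and two shortened arms that is 21·P(m) + 42·P(0.8m), where P is the share beyond day 14: 21 × 0.168 + 42 × 0.055 = 5.8 at (10, 0.35) and 21 × 0.350 + 42 × 0.173 = 14.6 at (12, 0.4), so about 6 to 15 of 63 under these assumptions. Data lock is slightly later.

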#### Quality of life

The Portuguese version of the MLHFQ will be used to assess the patient’s quality of life. The questionnaire provides a final score as a metric, and the change in score over the treatment period will be evaluated. The MLHFQ score is a measure of health-related quality of life in patients with heart failure. The higher the score, the greater the negative impact of heart failure on the patient’s quality of life. A score of 0 indicates that the patient has no limitations or problems related to heart failure, while a score of 105 indicates a maximum limitation or problem in all areas assessed by the questionnaire [18].

#### Funcional capacity

The TUG test will be performed to assess functional capacity. The patient will start from a sitting position, walk quickly for 3 meters, turn 180 degrees, and return to the chair. The time taken, measured from standing up to completely leaning the trunk against the chair, will be recorded. Time values below 10 seconds indicate maximum functionality, 10 to 19 seconds indicate functional independence, 20 seconds and above indicate some functional limitation, and 30 seconds and above indicate significant functional limitation [19].

#### Perception of change

The GPCS is a self-report tool that assesses an individual’s perception of change in a specific domain. It uses Likert-scale items ranging from "a very great deal worse/less" to "a very great deal better/more" to capture subjective information about perceived change [20].

#### Functional Independence Measure (MIF)

The MIF questionnaire will be administered preoperatively and on the sixth day to assess functional independence. Adaptado do questionário de Borges, 2006 [21].

#### Gasometric data

Includes pO2 (partial pressure of oxygen), pCO2 (partial pressure of carbon dioxide), HCO3 (bicarbonate), Arterial Oxygen Saturation (SaO2), and Base Excess (BE). These measurements will be collected on Day 1 and Day 2, following the ICU routine and based on the patient’s clinical needs.

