**Second outcomes:**

Score of the Minnesota Living with Heart Failure Questionnaire (MLHFQ) in Portuguese version, Funcional capacity, The global perception of change scale, The functional independence measure (MIF), pO2 (partial pressure of oxygen), pCO2 (partial pressure of carbon dioxide), HCO3 (bicarbonate), Arterial Oxygen Saturation (SaO2), Base Excess (BE), Presence of lung complications.

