## Introduction

Cardiovascular diseases are leading causes of both mortality and hospital admissions. Compared to other treatment modalities, cardiac surgery is distinguished by its advanced techniques and materials, which have led to safer procedures and reduced perioperative risks [1, 2].

In patients with cardiovascular diseases, including valvular disease, current guidelines advise considering exercise capacity for diagnosis and treatment planning [3, 4]. Moreover, coronary artery disease is the leading global cause of death, and patients undergoing coronary artery bypass surgery constitute a high-risk group [5]. Postoperative pulmonary dysfunction in patients undergoing cardiopulmonary bypass (CPB) is a significant clinical problem and has long been recognized by health professionals [6].

Postoperative pulmonary complications are highly prevalent, ranging from 5% to 20%, primarily due to perioperative factors and the intimate anatomical and functional relationship between the heart and lungs. These complications have been consistently associated with elevated postoperative morbidity and mortality rates [7, 8]. The etiology of pulmonary complications stems from a multifactorial process. Surgical factors like the use of cardiopulmonary bypass (CPB), anesthesia, surgical duration, mechanical ventilation duration, pleural opening, phrenic nerve alteration, use of mammary artery in myocardial revascularization surgery, sternal wound pain, and surgical drains lead to decreased functional residual capacity and increased intrapulmonary shunting. Furthermore, preoperative patient-related factors such as pre-existing lung diseases, smoking, advanced age, poor nutritional health, among others, predispose to complications [9].

Certain measures are employed during the postoperative period of cardiac surgeries to minimize pulmonary complications, including proper analgesia, oxygen therapy, and physiotherapy. Physiotherapy employs techniques such as deep breathing stimulation, cough stimulation, use of incentive spirometers, mobilization, and ambulation. However, at times these approaches fall short, and additional methods like Non-Invasive Ventilation (NIV) are employed [9].

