### Secondary objective

Describing the profile of cardiac patients undergoing cardiac surgery; outlining the patient profile concerning spirometry, Timed Up and Go (TUG) test, quality of life, The Global Perception of Change, vital signs, Functional Independence Measure (MIF), gasometric parameters, and pulmonary complications.

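### Oxygenation is defined as raw pO2 and SaO2 on Days 1–2, with no inspired-oxygen level or NIV status stated, so arm comparisons are hard to interpret and can describe only an early ICU effect

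*Protocol article*

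**What the plan says.** The abstract names the gas variables one by one as secondary outcomes: "pO2 (partial pressure of oxygen), pCO2 (partial pressure of carbon dioxide), HCO3 (bicarbonate), Arterial Oxygen Saturation (SaO2), Base Excess (BE), Presence of lung complications". The Gasometric data section repeats the same five gases, "Includes pO2 (partial pressure of oxygen), pCO2 (partial pressure of carbon dioxide), HCO3 (bicarbonate), Arterial Oxygen Saturation (SaO2), and Base Excess (BE", and fixes the sampling: "These measurements will be collected on Day 1 and Day 2, following the ICU routine and based on the patient’s clinical needs". FiO2, a pO2/FiO2 ratio, a fixed oxygen condition at the draw, and a record of whether NIV was running are not mentioned anywhere in the article.

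On exposure, the CPAP section states "This intervention will be administered for a duration of 5 days throughout the patient’s hospitalization, both in the ICU and general ward" and "The frequency of sessions will be twice (2 times) per day, in the morning and afternoon"; the BiPAP section gives the same schedule. The control-group section counts Day 1 as the first postoperative day and says that patients generally leave the ICU on Day 2.

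On use, the Secondary objective places the gases in a descriptive patient profile, ending with "gasometric parameters, and pulmonary complications". The Statistical analysis section plans a between-group comparison of the NIV effect over time by mixed models, without naming the outcomes to which it applies.

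**The concern.** Arterial pO2 and SaO2 depend on the lungs and also on how much oxygen the patient is breathing. If one patient has poorer gas exchange but receives more oxygen, the two can show the same raw values. A comparison of arms on raw pO2 or SaO2 then mixes any effect of NIV with differences in oxygen supply. Staff who apply the protocol are not blinded, so blinding does not ensure equal oxygen use across arms.

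The draw is also not tied to the NIV sessions. A sample in a CPAP or BiPAP patient may fall while positive pressure is being applied; in a control patient it cannot, unless NIV is given outside the protocol. A difference seen in such samples may end with the session.

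Finally, sampling stops on Day 2 of a five-day course. A reader could take the gas results as evidence on the whole course, which they are not. The Introduction gives better gas exchange as part of the rationale for NIV, so the meaning of these outcomes matters even though they are secondary.

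**Working it through.** The article states no figure for the gas outcomes that could be reproduced. The check has two parts.

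**1. Exposure at the last sample.** Inputs: 2 sessions a day and 5 days of NIV (CPAP and BiPAP sections); last sample on Day 2 (Gasometric data).

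- Full course: 2 × 5 = 10 sessions.
- Day 1 sample: after 0 to 2 sessions, or 0–20% of the course.
- Day 2 sample: after 2 to 4 sessions, or 20–40%.
- Sessions after the last day of sampling: at least 10 − 4 = 6.

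This counts Day 1 as the first postoperative day, as the treatment schedule does. The abstract also uses day 1 for the preoperative assessment. On that count, Day 2 is the day of surgery and at most 2 × 1 = 2 sessions could precede the end of sampling. So the bound of 4 of 10 holds on either reading, but the two uses should be reconciled.

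The CPAP and BiPAP sections plan a reassessment with the same instruments after the fifth day. They do not name blood gases, and the Gasometric data section gives the gases their own schedule, which ends on Day 2.

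**2. What a raw pO2 leaves open.** Formula: ratio = pO2 / FiO2. The article gives no FiO2 or pO2 values, so all of these are assumed:

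| FiO2 | ratio at pO2 100 mmHg | ratio at pO2 80 mmHg |
|---|---|---|
| 0.21 | 100/0.21 = 476 | 80/0.21 = 381 |
| 0.28 | 100/0.28 = 357 | 80/0.28 = 286 |
| 0.40 | 100/0.40 = 250 | 80/0.40 = 200 |
| 0.50 | 100/0.50 = 200 | 80/0.50 = 160 |

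At a fixed pO2, the two ratios differ by the factor FiO2(high)/FiO2(low), whatever the pO2. For 0.40 against 0.21 this is 0.40/0.21 = 1.90; for 0.50 against 0.21 it is 2.38; for equal FiO2 it is 1, and the problem disappears. These figures compare two hypothetical patients. They do not estimate a difference between arms, and the article offers nothing from which to estimate one.

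**Which outcomes are affected.** The oxygen-supply argument applies to pO2 and SaO2, two of the five gas variables. For pCO2, HCO3 and BE only the timing limit in part 1 is argued here.

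**The case against.** There are four serious objections.

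- **No oxygen rule is stated.** The only mention of oxygen therapy, "including proper analgesia, oxygen therapy, and physiotherapy", is background in the Introduction about care after cardiac surgery in general. The usual-care schedule lists exercises and does not mention oxygen. This stands: one might infer that oxygen is adjusted to saturation here and so masks a real effect, but the article does not show it. Unequal oxygen supply must be treated as an assumption.
- **The article is condensed.** The list opens with a word that need not close it, and the fields recorded beside a blood gas may be in the full protocol. This stands for the recording of FiO2 and NIV status. It does not remove the point, because the outcomes themselves are named as raw pO2 and SaO2. FiO2 kept on a form would not change what is compared.
- **An early outcome is legitimate.** A reader might infer that the gases are meant to show whether the five-day course improves oxygenation and that the plan fails at this. No section says so. The sampling days are stated openly, they match the usual ICU stay, and the secondary objective is descriptive. Pulmonary function, a primary outcome, is reassessed at the end of the course. This stands, and it reduces the timing point to one of labelling.
- **A fixed draw would be a poor remedy.** Requiring a Day 2 sample before that day's first session would lower exposure to at most 2 of 10 sessions and would conflict with sampling by routine and need. This stands, and no new draw time is proposed.

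**Conclusion.** The concern holds in a limited form. As defined, the oxygenation outcomes depend on oxygen supply and on NIV status at the draw as well as on gas exchange, and the article states neither beside them. If FiO2 differs, the same pO2 can correspond to ratios that differ by a factor of 1.90 (0.21 against 0.40) or 2.38 (0.21 against 0.50); if it does not differ, nothing is lost. The size and direction of any bias between arms are unknown. Samples taken during NIV could add a transient difference.

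The timing limit needs no assumption: at most 4 of 10 sessions precede the last gas sample, so all five variables can speak only to an early ICU effect. It would be too strong to say that the gas outcomes are invalid, or that the plan misuses them to judge the full course. They are secondary outcomes, and the weakness is inexpensive to repair.

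**What to change.** 1. With each routine blood gas already taken, record FiO2 (or oxygen flow and interface) and whether NIV was running.
2. Make pO2/FiO2 the oxygenation outcome compared between arms, and keep raw pO2 and SaO2 as descriptive values.
3. Account for NIV on/off status in the comparison, for example by a sensitivity analysis restricted to samples drawn off NIV. Impose no new draw time.
4. Report all gas results as early effects, on Days 1–2.

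The cost is two form fields, one derived variable and a change of label; no extra samples are needed. There are two downsides. FiO2 is only approximate on low-flow devices, so the ratio will carry some measurement error. The off-NIV restriction may lose samples, and because it selects on something that happens after randomisation, it should stay a sensitivity analysis and not replace the main comparison.
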